### Interventions

The flow chart of the study is given in Fig. 1. The program will contain the following intervention elements:Parents will commit to spending at least 6 h per day in the NICU providing care for their children;Parents will provide the majority of non-medical care for their infants, including feeding, bathing, dressing, changing diapers, giving oral medications, and developmental care, such as skin-to-skin care;Parents will attend regular education sessions to learn the skills necessary to provide care for their infants;Parents will maintain records of their infants’ progress, including temperature and weight gain, and attend rounds to discuss their infants’ care with the medical staff;Nurses will work with parents to support and educate them;A training program will be provided for nurses so that they are provided with the tools to support program implementation and act as coaches for parents;Each NICU will provide physical supports, such as comfortable chairs at the infant’s bedside and a rest area for parents, and develop policies that support parents’ ability to spend at least 6 h in the NICU.

**Fig. 1 Fig1:**
[figure not shown]
Flow chart of study design. This is a cluster randomized control trial about family integrated care (FICare) in China. This 3-year research is divided into two stages: an internal pilot study (1 year) and a main study (2 years). Ethical approval will be obtained first, followed by recruitment of research collaborator. After basement data collection, six level III NICUs in different tertiary hospitals will be randomly divided into two groups: the FICare group and the control group. Questionnaires about the demands of and attitude to FICare, and recruitment lectures about FICare will be completed in the early stage of the internal pilot study. A small number of patients will be enrolled in the internal pilot study. The data in the internal pilot study will be used to re-adjust the final sample size. Primary outcome measure data and secondary outcome measure data will be collected in both the internal pilot study and the main study. Data will be statistically analyzed at the end of the whole study

### Data collection procedures

A central research coordinator based at Central South University will be in charge of organizing data collection in each NICU. At least four post-graduate students will also be involved in collecting data. A research nurse at each participating NICU will be designated to work with the research coordinator and collect data. Data on maternal and infant outcome measures will be collected from patient charts using a predesigned form. The data will then be entered into a computer database along with information gathered from parents and nurses using questionnaires. Completed questionnaires will be kept in a locked cabinet at each site, accessible only by the site investigator, and the database will be password protected and accessed only by the designated research nurse at each site. The research coordinator will send the data electronically to specialists for statistical analysis every 3 months, make monthly summaries of progress and update both participating parents and the study principle investigators, organize parent activities, and obtain feedback from parents.

The clinical data to be collected are: (1) characteristics of patients: birth weight, gestational age, sex, Cesarean section, maternal gestational hypertension, maternal gestational diabetic mellitus, prolonged pre-rupture of membrane >18 h, Apgar score at 5 min after birth, SNAPPE-II (Score for Neonatal Acute Physiology–Perinatal Extension-II), antenatal steroid usage, pulmonary surfactant usage, period of intubation for invasive ventilation, period of non-invasive ventilation, period of oxygenation, age of starting enteral feeds; (2) research parameters: mortality rate, rate of breast feeding, weight gain and growth speed, time to full feeds, infection rate and infection incidence per 1000 hospitalization days, total hospitalization period, total medical hospitalization expense, extra expenses of medical staff, re-admission rate within 30 days after discharge home, parents’ questionnaire (including parental confidence in taking care of their infant and parents’ stress related to having a hospitalized infant).

The primary outcome measure is the total hospitalization period. The secondary outcome measures are: total medical expenses, infection incidence per 1000 hospitalization days, rate of breastfeeding, parental confidence and stress, assessment of feasibility and necessity of model of care, development of guidelines for supervising parents participating in the FICare model in the NICU.

The key independent variables are: rate of breast feeding, weight gain and growth speed, infection incidence per 1000 hospitalization days, total hospitalization period. The extra expenses for medical staff will include: salary for the hired research nurse, stipend for engaging doctors and nurses for extra hours of work related to the study (compared with the control groups), expenses for preparing parent education materials.

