### Hypotheses

The primary hypothesis is that the implementation of the FICare model for preterm infants in Chinese NICUs will result in a significant reduction in nosocomial infection and hence length of hospitalization. The secondary hypotheses are: (1) implementation of the FICare model in Chinese NICUs will improve maternal and infant outcomes including infant weight gain, maternal stress, and breastfeeding rates; (2) implementation of the FICare model in Chinese NICUs will result in decreased total medical expenses for preterm infants.

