### Data analysis

Data analysis will be conducted on an intention-to-treat basis. To take into account the clustering effect, Student’s *t* test adjusted for the inflation factor (or design effect) [11, 12] will be used, to compare the primary outcome between the FICare and control groups. Furthermore, a two-level hierarchical linear regression model will be used to compare the primary outcome measure between the two groups, accounting for patient-level characteristics, such as gestational age, small for gestational age, sex, Apgar score at 5 min, maternal age, delivery mode, maternal hypertension, chorioamnionitis, maternal education, and the NICU-level covariates (NICU size, number of nurses, and neonatologists). To take into account the cluster effect, a symmetric covariance matrix structure will be used for the models.

The secondary outcome measures will also be compared between the two groups using Student’s *t* test for continuous variables and the chi-square test for categorical variables adjusted for the inflation factor. A two-level hierarchical linear regression model or a logistic regression model, as appropriate, will be applied for the comparison of the outcomes between two groups, accounting for patient-level and NICU-level characteristics.

To assess the rate of growth for the two groups, we will further examine the rate of weight change over time, if applicable. Linear or nonlinear mixed-effect models for longitudinal data will be used to compare the rate of change in weight gain between the two groups, adjusted for duration of hospital stay, and patient-level and NICU-level characteristics. An interim analysis for the internal pilot study will first be conducted using similar methods, if applicable. The preliminary results will then be used to re-justify the sample size, using the method of Lake et al. [10].

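### Infection is listed as a rate per 1000 hospital days, but the tests and models fixed for secondary outcomes include none suited to events over unequal time at risk

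*Protocol article*

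**What the plan says.** The Hypotheses section expects that FICare "will result in a significant reduction in nosocomial infection and hence length of hospitalization". The Data collection procedures section makes total hospitalization the primary outcome. Its list of secondary outcomes gives infection in one form only, as an incidence per 1000 hospital days: "The secondary outcome measures are: total medical expenses, infection incidence per 1000 hospitalization days, rate of breastfeeding, parental confidence and stress". The same section says that the trial collects both "infection rate and infection incidence per 1000 hospitalization days". It does not define the first of these and does not carry it into the outcome list. The Abstract mentions nosocomial infection as an example of a secondary clinical outcome, without a measure.

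The Data analysis section then fixes the methods for secondary outcomes: Student's t "test for continuous variables and the chi-square test for categorical variables adjusted for the inflation factor", followed by regression: "A two-level hierarchical linear regression model or a logistic regression model, as appropriate, will be applied", with adjustment for patient-level and NICU-level characteristics. The only further models named, linear or nonlinear mixed-effect models, are for weight over time. No count or person-time model is named.

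**The concern.** An incidence per 1000 days divides events by time at risk, and time at risk differs widely between infants: the plan assumes a mean stay of 28 days with an SD of 15. The stated methods leave two ways to handle it at infant level. One is to compute a rate for each infant and treat it as continuous. The other is to reduce infection to yes or no. The first gives a mostly zero, strongly skewed variable in which a short stay counts as much as a long one. The second ignores the days that define the outcome.

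What is at stake is how the infection result can be read. The Background gives infection control as one reason why parents are kept out of Chinese NICUs, and the trial is meant to inform that policy. The infection comparison will therefore be read closely even though it is secondary. The plan also expects FICare to shorten stay, so the rate and the per-infant proportion can move differently, and only the rate is a defined outcome.

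**Working it through.** **Inputs.** From Sample size calculation: mean stay 28 days, SD 15, expected fall 5 days (to 23), ICC 0.01, 10% drop-out, 293 infants per group, 98 per hospital. From Background: 11.6% nosocomial infection in mainland NICUs, used here only as an illustrative number of infections per infant. Assumed: two-sided 5% alpha, because none is stated.

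**1. The plan's own figure.** Unadjusted n per arm = 2 × [15 × (1.960 + 0.842) / 5]² = 141.3. With about 88 evaluable infants per NICU (98 × 0.9), the design effect is 1 + 87 × 0.01 = 1.87. Then 141.3 × 1.87 / 0.9 ≈ 293.5, against 293 stated. The sample size for stay reproduces, and nothing below rests on it.

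**2. Outcome against methods.**

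| Stated method | What it would use | Handles unequal days? |
|---|---|---|
| t test, two-level linear model | each infant's infections / days | No: all infants weighted alike |
| Chi-square, two-level logistic | infected yes/no | No: days dropped |

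**3. Shape of the infant-level rate.** One infection in a 10-day stay scores 1/10 × 1000 = 100; in a 40-day stay it scores 1/40 × 1000 = 25; no infection scores 0 at any length of stay. I simulated gamma-distributed stays (mean 28, SD 15, floor 7 days) with Poisson infections at a constant hazard of 0.116/28 = 4.14 per 1000 days and no clustering. About 89% of infants had a rate of zero; the mean was about 4.2 and the SD about 14 per 1000 days.

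**4. What equal weighting does.** Write λ for the daily hazard and d for an infant's days. The variance of an infant's rate is λ/d.
- *Constant hazard.* The unweighted mean of n infant rates has variance λ·E[1/d]/n; the pooled rate (all infections over all days) has λ/(n·E[d]). Their ratio is E[d] × E[1/d] = 28.05 × 0.0481 ≈ 1.35 for the simulated stays. Both target the same rate, but the unweighted mean has about 35% more variance.
- *Infections not proportional to stay* (0.116 per infant whatever the stay). The two no longer target the same quantity. At mean 28 days the pooled rate is about 4.1 and the mean of infant rates about 5.6; at mean 23 days they are about 5.0 and 7.3. The between-arm ratio is then about 1.21 pooled and about 1.30 unweighted. (The floor on stay moves the pooled ratio slightly off 28/23.)

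**5. Rate and proportion answer different questions.**
- *Infections per infant unchanged, stay 28 to 23 days.* The rate goes from 0.116/28 = 4.14 to 0.116/23 = 5.04 per 1000 days, a ratio of 28/23 = 1.22 that does not depend on the 11.6%. Infections per infant would have to fall to 23/28 = 0.82 of the control value for the rates to be equal.
- *Daily hazard unchanged, stay 28 to 23 days.* The rate stays at 4.14, while expected infections per infant fall from 0.116 to 0.00414 × 23 = 0.095.

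**6. Counting from enrolment.** If 7 days precede enrolment in both arms (assumed; no figure is given), the first case in step 5 becomes (28 − 7)/(23 − 7) = 21/16 = 1.31. Counting from enrolment confines the comparison to time when FICare can act, but does not remove the dependence on stay.

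**The case against.** The best defence is that incidence per 1000 days is an ordinary surveillance measure, that the article leaves the choice of model to what is appropriate, and that details belong in an analysis plan not shown. Part of this stands. The measure is legitimate, and a t test on six NICU-level rates would be a valid cluster-level analysis. Logistic regression would suit a per-infant infection outcome if one were defined. But the stated choice is between linear and logistic only, and the tests are infant-level ones corrected by an inflation factor. That is a method stated for secondary outcomes that does not fit this one, not a gap left for later.

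Several stronger readings are tempting and are not supported:

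- *A benefit would be reported as harm.* The 1.22 requires that the days removed by FICare carry almost no infection risk. Nothing in the article says so, and at a constant daily hazard the rate does not move.
- *An offset model cures the dependence on stay.* It keeps the same denominator; step 6 shows the illustrative ratio growing when days run from enrolment.
- *The per-infant proportion is free of length of stay.* Fewer days at risk mean fewer infections, as the second case in step 5 shows.
- *Infections before enrolment are counted.* The article does not say when the numerator or the clock starts. This is an inference, and such detail may sit in the full protocol.
- *Infection is a second primary endpoint, or is underpowered.* The phrase "significant reduction in nosocomial infection and hence length of hospitalization" can be read as naming infection as the mechanism. The Abstract, Sample size calculation and Data collection procedures all make stay the primary outcome. A secondary outcome need not be powered.

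**Conclusion.** The concern holds as a mismatch between one listed outcome and the methods fixed for it. No infant-level method in the Data analysis section properly estimates infections per 1000 hospital days. Under the assumptions above, the infant-level rate is about 89% zeros with an SD more than three times its mean. Averaging it without weights costs about 35% in variance at a constant hazard, and targets a different quantity when infections do not scale with stay. These figures rest on the borrowed 11.6%, a gamma shape for stay, a 7-day floor and no clustering. The factor 28/23 = 1.22 rests only on the plan's two mean stays and on infections per infant being unchanged; it illustrates how the two measures part and does not predict a result.

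The point is confined to a secondary outcome. The analysis of stay and the sample size stand. It is still worth correcting, because the remedy is cheap and infection is central to the policy question.

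**What to change.** In the Data analysis section, take infection incidence out of the general rule for secondary outcomes. Analyse it with a Poisson or negative-binomial model with log(days at risk) as offset and inference suited to six NICUs, or compare NICU-level rates at cluster level. Count infections and days from enrolment where chart dates allow, and state the window.

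Define the infection rate already collected as the proportion of infants with at least one infection, list it as an outcome, and report it with clustering-adjusted logistic regression. State that the two measures answer different questions: the rate describes daily hazard, and the proportion describes cumulative risk, including the effect of length of stay. Interpret them together.

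The cost is a little more analysis work and the extraction of infection dates from the charts. No more infants are needed.

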### Data analysis

Data analysis will be conducted on an intention-to-treat basis. To take into account the clustering effect, Student’s *t* test adjusted for the inflation factor (or design effect) [11, 12] will be used, to compare the primary outcome between the FICare and control groups. Furthermore, a two-level hierarchical linear regression model will be used to compare the primary outcome measure between the two groups, accounting for patient-level characteristics, such as gestational age, small for gestational age, sex, Apgar score at 5 min, maternal age, delivery mode, maternal hypertension, chorioamnionitis, maternal education, and the NICU-level covariates (NICU size, number of nurses, and neonatologists). To take into account the cluster effect, a symmetric covariance matrix structure will be used for the models.

The secondary outcome measures will also be compared between the two groups using Student’s *t* test for continuous variables and the chi-square test for categorical variables adjusted for the inflation factor. A two-level hierarchical linear regression model or a logistic regression model, as appropriate, will be applied for the comparison of the outcomes between two groups, accounting for patient-level and NICU-level characteristics.

To assess the rate of growth for the two groups, we will further examine the rate of weight change over time, if applicable. Linear or nonlinear mixed-effect models for longitudinal data will be used to compare the rate of change in weight gain between the two groups, adjusted for duration of hospital stay, and patient-level and NICU-level characteristics. An interim analysis for the internal pilot study will first be conducted using similar methods, if applicable. The preliminary results will then be used to re-justify the sample size, using the method of Lake et al. [10].

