### Randomization

Since the intervention could not be completely blinded in this study, we choose a cluster randomized controlled trial design in which hospitals are randomized into two groups (intervention and control groups) instead of patients, to avoid contamination of patients in control groups. Since only six are NICUs participating in this study, the randomization was completed by a method of drawing lots by two third-party persons who are blinded to this project. In detail, the name of each participating hospital was written a piece of paper and put into an envelope by a person who was not aware of this project. The six envelopes were identical. Another person who was also blinded to this project randomly divided the six envelopes into two groups (the intervention group and the control group), with three NICUs in each group.

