### Sample size calculation

The proposed sample size is based on the primary outcome of duration of hospital stay. From our previous clinical data and similar clinical research reports from our Canadian colleagues [9], the average duration of hospital stay is 28 days with a standard deviation of 15 days. We expect a decrease in hospital stay of 5 days (an approximate 18 % decrease) in the FICare group compared with the control group. Based on this expectation, the sample size was estimated using the method of Lake et al. [10], assuming an intra-cluster correlation coefficient of 0.01. We estimate that a total sample size of 586 (293 for each group or 98 for each hospital) will achieve a power of 80 % to detect the expected 18 % decrease in duration of hospital stay in the FICare group compared with the control group, taking into account a 10 % drop-out rate following enrollment in the study. This sample size will be re-adjusted in the interim analysis at the completion of the pilot study.

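### The planned tests of hospital stay are not tied to the six randomized NICUs; under the usual reference distribution the scaled t test rejects a true null about 8% of the time at the plan's ICC, and up to about 12% at larger ICCs

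*Protocol article*

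**What the plan says.** The Randomization section of the protocol article allocates six hospitals by drawing lots, "with three NICUs in each group". Setting and sample adds that the six come as two per city in three cities, and that the NICUs within an arm come from different cities.

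For the primary outcome, Data analysis names a Student's t test, described as "adjusted for the inflation factor (or design effect) [11, 12] will be used, to compare the primary outcome between the FICare and control groups". It then adds that "a two-level hierarchical linear regression model will be used to compare the primary outcome measure between the two groups", with a list of patient-level characteristics and "the NICU-level covariates (NICU size, number of nurses, and neonatologists" as NICU-level terms, and that "a symmetric covariance matrix structure will be used for the models". Secondary outcomes receive the same scaled t test or "the chi-square test for categorical variables adjusted for the inflation factor", followed by linear or logistic hierarchical models.

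The section gives no df, no small-sample correction and no choice between REML and ML. It does not say whether the inflation factor uses an estimated ICC or the planning value of 0.01, or which of the two primary-outcome analyses decides the trial.

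**The concern.** The between-NICU variance governs the precision of the arm comparison, and it can be learned only from six units. A t or chi-square statistic computed on infants and then divided by an inflation factor is ordinarily still referred to several hundred infant-level df. The usual Wald test from a mixed model likewise uses a normal reference. Both treat the between-NICU variance as if it were known. Intervals then come out too narrow, and a nominal 5% test can reject too often.

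The hierarchical model adds a second difficulty that is written into the text: an intercept, the arm and three NICU-level covariates use five of the six NICU-level df.

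At stake is the error rate of the trial's main claim, which the article hopes will inform NICU policy across China, and the power figure that the sample-size re-adjustment after the pilot will carry forward.

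**Working it through.** **Inputs.** From Sample size calculation: "the average duration of hospital stay is 28 days with a standard deviation of 15 days"; an expected effect of 5 days, about 18% of the mean; ICC 0.01; power 80%; drop-out 10%; 586 infants in total, 98 per hospital. From Randomization: 3 + 3 NICUs. The significance level is not stated; two-sided 0.05 is assumed.

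**Step 1: the plan's own sample size.**
- Per arm without clustering: 2 × (1.96 + 0.8416)² × 15² / 5² = 141.3.
- Evaluable infants per NICU: 98 × 0.9 ≈ 88.
- Design effect: 1 + (88 − 1) × 0.01 = 1.87.
- Per arm: 141.3 × 1.87 = 264.2; divided by 0.9 = 293.5, or 587 in total against 586 stated.

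The plan's figure is reproduced with normal quantiles, so it contains no allowance for having only six clusters.

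**Step 2: df between NICUs.**
- Arm comparison alone: 6 − 2 = 4.
- With three NICU-level covariates: 6 − 5 = 1.

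**Step 3: type I error of the scaled t test.** Simulation: 400,000 trials per setting, 3 + 3 NICUs, 88 infants each, normal outcome, no arm effect, no city effect. Between-NICU variance is 225 × ICC, and the within-NICU variance of a mean is 225 × (1 − ICC)/88. "Estimated" below means a within-arm ANOVA ICC truncated at 0.

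| True ICC | ICC estimated, N − 2 df | Factor fixed at ICC 0.01 | Six NICU means, 4 df |
|---|---|---|---|
| 0 | 3.7% | 0.7% | 5.0% |
| 0.005 | 6.3% | 2.5% | 5.0% |
| 0.01 | 8.1% | 5.1% | 5.0% |
| 0.02 | 10.1% | 10.7% | 5.1% |
| 0.05 | 11.7% | 24.9% | 5.0% |
| 0.10 | 12.3% | 39.8% | 5.0% |

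With 98 infants per NICU the estimated-ICC column reads 8.5% at 0.01 and 12.4% at 0.10. The analytic value without truncation is P(|t₄| > 1.96) = 12.2%.

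**Step 4: the hierarchical model.** Without NICU-level covariates, a REML Wald z test behaves like the scaled t test (8.1% at ICC 0.01, 12.0% at 0.10). With three simulated NICU-level covariates (100,000 trials, 88 per NICU), REML Wald error is 10.1% at ICC 0.01, 14.4% at 0.02, 20.9% at 0.05 and 24.9% at 0.10. Under ML the range is 15.2% to 44.6%.

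**Step 5: a shared city effect.** If each city supplies one NICU to each arm, city differences cancel from the arm contrast but stay in the within-arm variance. Taking half of the between-NICU variance as city (an assumption), the scaled t test with estimated ICC errs about 5% of the time at ICC 0.01 and about 6% at 0.05. With 80% as city it errs about 3% of the time. The unpaired 4-df test then also becomes conservative: 3.5% and 2.5% at ICC 0.01 and 0.05 with a half share.

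**Step 6: power once the df reflect six NICUs.** The standard error is 15 × √(2 × 1.87 / (3 × 88)) = 1.785 days, so the noncentrality is 5/1.785 = 2.80.
- Normal reference: 80%.
- 4 df, critical value 2.78: 56%.
- 98 infants per NICU (design effect 1.97, standard error 1.736, noncentrality 2.88), 4 df: 59%.
- City-paired test, 3 − 1 = 2 df, critical value 4.30, no city effect: 35% (88 per NICU) to 37% (98 per NICU). Any city variance removed by pairing would raise this.

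**The case against.** The strongest reply is that the article does not state the df. It is a condensed protocol, the adjusted t test is defined in cited references, and an unseen analysis plan could prescribe NICU-based df. That stands as a limit on the claim: a reader might infer that the protocol fixes infant-level df and so has an 8% to 12% error rate as a fact, and the text does not support that. The rate follows from the usual application of the named test.

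Other readings give other figures at ICC 0.01: 5.1% with the factor fixed at the planning value, and 1.9% if the ICC is estimated across all six NICUs ignoring arm. Below ICC 0.01 the inflation shrinks or disappears, and a shared city effect under pairing reduces it further. All of this stands. It also shows that the error rate depends on choices that the text leaves open.

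Two further inferences go too far. One is that every secondary outcome has an inflated error rate. Only a continuous outcome with normal data was simulated, and some listed secondary outcomes, such as feasibility assessment and guideline development, are not obvious candidates for a test. The same reasoning on df applies to those that are tested, but its size there is not established. The other is that the two primary-outcome analyses are declared equal. The t test comes first, and the Discussion gives the multilevel model the role of adjusting for confounders. What can be said is that neither is named as decisive.

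The objection does not remove the core. A scaled infant-level test and three NICU-level covariates on six clusters are stated methods, not details left for later.

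**Conclusion.** The point holds as a conditional one. With a two-sided 5% level, infant-level or normal reference, ICC estimated within arms, equal NICU sizes, normal data and no city effect, the scaled t test rejects a true null about 8% of the time at the plan's ICC of 0.01 and up to about 12% by ICC 0.10. With the factor fixed at 0.01, the test is correct only if that ICC is correct, and errs about 25% of the time at 0.05. The hierarchical model as written, with a REML Wald test, errs about 10% to 25% of the time over ICCs of 0.01 to 0.10, which is worse than the t test it supports.

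The stated sample size is not an arithmetic error. Its 80% power, however, belongs to a test that treats the between-NICU variance as known. With 4 df the power for 5 days at ICC 0.01 is about 56% to 59%.

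**What to change.** 1. Name one primary analysis whose df come from the six NICUs. One workable form is to adjust stay for the patient-level covariates and then compare the six adjusted NICU means with a t test on 4 df.
2. Reconcile Setting and sample, which implies one NICU per arm in each city, with Randomization, which describes an unrestricted division of six envelopes. If allocation was paired by city, a city-paired version of the test (2 df) is the alternative, and the choice between the two should be fixed before the arms are compared.
3. Keep the mixed model as supportive, with a small-sample df correction such as Satterthwaite or Kenward-Roger and without the three NICU-level covariates. The Discussion, which also promises that adjustment, needs the same change.
4. If an inflation-factor test is retained anywhere, state where its ICC comes from and use NICU-based df.
5. Use NICU-based df for the secondary outcomes that are tested.
6. Restate the power, and carry the same df into the sample-size re-adjustment.

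**Cost.** The edits are to wording and need no new data. The real price is precision: the critical value rises from 1.96 to 2.78, intervals widen accordingly, and power for the 5-day effect is about 56% to 59% on 4 df, and lower on 2 df unless pairing removes substantial city variance. Dropping the NICU-level covariates means that differences in size and staffing can be described but not adjusted for.
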